### 2.6. Ethics Approval and Consent to Participate

This study follows the Code of Ethics of the Declaration of Helsinki [99], and it will comply with the applicable national and EU legislation on ethical principles, privacy and data protection. More specifically, it will comply with (a) Directive 2002/58/EC on the processing of personal data and protection of privacy in the electronic communications sector (Directive on privacy and electronic communications) of the European Parliament and of the Council of 12 July 2002, and the (b) EU Regulation 679/2016 on the protection of natural persons with regard to the processing of personal data and on the free movement of such data, and repealing Directive 95/46/EC (General Data Protection Regulation). All researchers involved in the study will sign a confidentiality statement before recruitment or enrolment of pregnant women in the study. A referral plan will be developed to assist researchers in referring women to health services during the project whenever necessary. All participants will be asked to sign a data agreement form and an informed consent form (ICF) before their and of their babies enrolment in the study. The later document will include a detailed explanation of the objectives and methods of the study, as well as their right to refuse or quit their participation at any time. Women who agree to participate in the study also agree with their babies’ participation as stated in the ICF. Delphi panel members will also be asked to read and, in case of agreement, to sign an ICF before their enrolment in the study. Participants will receive the devices for physiological data collection free-of-charge.

The research protocol was approved by the Ethics Committee of the Lisbon Academic Medical Centre of the University of Lisbon. Selection and recruitment of participants will only start after the ethical approval of the Regional Health Administration of Lisbon and Tagus Valley and of the administration board of each healthcare unit. Data confidentiality will be guaranteed and its access will only be granted to team members of the MAMH@WORK project.

## 3. Discussion

The transition to motherhood encompasses numerous changes that require continuous psychosocial adjustment. This places mothers-to-be and recent mothers at an increased risk of developing mental disorders [2,3,4]. At the same time, the perinatal period is a window of opportunity for promoting women’s health/wellbeing and enhancing mother-infant relationships, since these aspects are routinely monitored by healthcare professionals. Here we describe a community-based randomized study protocol to assess the effectiveness of a CBT-based psychoeducation intervention, with or without a biofeedback system, targeting pregnant women at the time of recruitment. MAMH@WORK goes beyond similarly-themed projects (e.g., [100,101]) by adopting an integrated approach in which mother–child relationship, child behavioral, and emotional and cognitive regulation development are addressed, and so is the return to work. Moreover, traditional methods for effectiveness assessment of the intervention are combined with technology-driven approaches providing women with biofeedback on selected physiological indicators. Taking this into consideration, MAMH@WORK emerges as a strategic project for the prevention of mental disorders and for the promotion of mental health and wellbeing during a very challenging period for women and their spouses. Importantly, the intervention will be delivered by trained psychiatrists and psychologists who will follow the referral plan whenever needed, thus contributing for no relevant risks of this intervention to the mother and her child.

Several challenges are anticipated. Recruitment of pregnant women will take place at two different settings (primary health care units and private clinics) and thus, two distinct sociodemographic groups are expected to be enrolled, namely, in terms of their income: pregnant women from high income families have the financial capacity to pay for obstetric appointments at a private clinic, whereas women from low income families will mainly be followed during pregnancy at primary health care centers and public hospitals. Thus, the added-value of this intervention must be stratified according to socioeconomic characteristics. In addition, since the assessment of effectiveness requires repeated measures through time, several strategies to reduce attrition are planned (e.g., periodic telephone contacts, a webpage for project-related communication purposes, and a smartphone app). 

This is a small-scale project to be conducted in the Lisbon Metropolitan Area, and thus it will not mirror the Portuguese reality as a whole. However, if it proves effective in the promotion of maternal mental health/wellbeing, we will scale-up MAMH@WORK to the nation-wide level by establishing a strong network with primary healthcare units and obstetricians from other Portuguese metropolitan areas. This would also contribute to the sustainability of the project beyond its closure, in tandem with several other actions that are planned to ensure that the outcomes can be used after the project ends. For example, expected results will contribute to bring together several stakeholders, including healthcare professionals (i.e., general practitioners, obstetricians, psychiatrists, psychologists, and nurses), employers, and organizational leaders, and it will ultimately inform policy makers and support the elaboration of policy briefs regarding work–life balance and perinatal mental health promotion in the workplace. In addition to policy briefs, a training program on perinatal mental health and organizational leadership styles supporting healthy workplaces will be specifically designed for staff at all levels within the organizations (top-level leaders, intermediate-level leaders, employees). The latter will include a good practices manual for mental health promotion at the workplace. 

## 4. Conclusions

Overall, the expected impacts of MAMH@WORK project will ultimately contribute to meet national and international strategic goals. These include (a) to implement mental health promotion programs and to set early childhood and adolescence mental health as a priority in health agendas, as disclaimed in the current Portuguese National Mental Health Plan [102], (b) to increase health gains in the workplace by monitoring and promoting mental health, as well as to promote healthy workplaces, as defined in the current Portuguese National Occupational Health Plan [103], (c) to promote overall health and wellbeing of women and their children in a sensitive phase of their lives, which is in line with the EU Horizon 2020 societal challenges and the UN Sustainable Development Goal 3 (SDG 3), (d) to empower women and promote their participation in the labour market (SDG 1, SDG 5), with a potential positive impact in fertility rates, and finally, (e) to support smart, sustainable and inclusive economic growth (SDG 8) as outlined in the Europe 2020 Strategy by the European Commission [104].

## Figures and Tables

**Figure 1 ijerph-18-02558-f001:**
[figure not shown]
Schedule of enrolment, interventions and assessments of MAMH@WORK project following SPIRIT 2013 checklist.

**Table 1 ijerph-18-02558-t001:** Instruments to be used in the effectiveness assessment of the intervention.

Questionnaire/Measure Scale	Description	Timing of Assessment
Mental Health Literacy		
Mental Health Literacy Scale (MHLS) [72]	MHLS is a 35-item questionnaire that assesses six attributes of mental health literacy: recognition of disorders, knowledge on how to seek mental health information, knowledge on risk factors and causes, knowledge of self-treatment, knowledge of professional help available, and attitudes that promote recognition and appropriate help-seeking. High scores indicate high levels of mental health literacy. Instrument validated for the Portuguese population [73].	Pregnancy Postpartum
**Psychological Wellbeing, Resilience and Stress-related Coping Style**		
Hospital Anxiety and Depression Scale (HADS) [74]	HADS is a 14-item screening tool composed of two subscales, one for anxiety and other for depression. High scores indicate the presence of a mood disorder. Instrument validated for the Portuguese population [75].	Pregnancy
Edinburgh Postnatal Depression Scale (EPDS) [76]	EPDS is a 10-item questionnaire that screens for depression in pregnant women and during the first postpartum year. Depressed women score high in EPDS. Instrument validated for the Portuguese population [77].	Postpartum
Kennerley Blues Scale (KBS) [9]	KBS is an 18-item screening tool for postpartum blues. Women are asked to rate current emotions according to how different they feel compared to usual. It is composed of seven clusters: primary blues, reservation, hypersensitivity, depression, despondency, retardation, and decreased self-confidence.	Postpartum
Connor–Davidson Resilience Scale (CD-RISC) [78]	The original CD-RISC is a 25-item scale that measures resilience as the ability of overcoming adversity and stress coping ability. Two shorter versions of this scale are authorized for use, CD-RISC-10 and CD-RISC-2. CD-RISC-25 [79] and CD-RISC-10 [80] have been validated for the Portuguese population. In this study, either the CD-RISC-10 or the CD-RISC-2 (to be validated in this study if applicable) will be used.	Pregnancy Postpartum
Stress-Related Coping Style (BRIEF COPE) [81]	The BRIEF COPE characterizes coping styles and strategies following Lazarus & Folkman’s model [82] and the behavioral self-regulation model.	Pregnancy Postpartum
Self-Report on Happiness [83]	Self-report single-item on happiness to be measured in a daily basis via the smartphone application.	Pregnancy Postpartum

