### 2.2. Sampling Details and Characteristics of the Sample

The target population of this mental health promotion project are pregnant women living in Portugal, with no diagnosis of depression, and employed at the time of recruitment. Women will be recruited at 28–30 weeks of gestational age, since antenatal depression is a relevant predictor for PPD [65,66]; thus, the potential effectiveness of the intervention should increase if it starts during pregnancy. All women booked for delivery at Portuguese hospitals attend various antenatal routine appointments in primary and secondary health care units, which are intended to reduce complications during pregnancy and to improve the chances of positive pregnancy outcomes. These appointments also serve for counselling about health behaviors during the antenatal and postpartum periods. Recruitment will take place in the Lisbon Metropolitan Area from three primary health care units and a network of private clinics. Women at 28–30 weeks of gestation attending an antenatal routine appointment will be invited, by their doctors or nurses, to participate with their babies in the study according to inclusion and exclusion criteria detailed below. In case of agreement, women will be asked to sign a data agreement form and will later receive a formal invitation addressed by the research team. To assess their eligibility to be enrolled in the study, women will be presented with a screening questionnaire conducted by trained psychiatrists and psychologists. In addition, clinical inclusion and exclusion criteria, namely serious mental disorders diagnosed, will be evaluated by antenatal healthcare professionals (i.e., general practitioners, obstetricians, psychiatrists, and psychologists).

To be enrolled in the study, women must meet the following inclusion criteria: native Portuguese speakers or women living in Portugal for at least 5 years; intended pregnancy; primiparous, singleton pregnant women at gestational age of 28–30 weeks; aged 18–40 years; employed; eligible for maternal leave; with access to a smartphone; and have had understood and signed the project’s informed consent form.

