### 2.4. Data Collection and Variables under Study

Data collection will be performed through self-administered questionnaires, wearable devices for biomonitoring physiological signals (in association with a smartphone app), and direct observations of mother–child interactions. It will be conducted on five different moments (Figure 1): baseline (t_0_; 28–30 gestation weeks), one week after enrolment (t_1_; 29–31 gestation weeks), two weeks postpartum (t_2_), five months postpartum (t_3_), and twelve months postpartum (t_4_). Data collection will be performed by members of the research team. Women in the intervention group with biofeedback will wear a smartwatch to biomonitor several physiological signals combined with the use of a sleep analyzer device (for details, see Table 1). Both devices will communicate through Bluetooth with a datahub and send physiological data to the supplier’s cloud. The server will communicate on a regular basis, via a secure oAuth2 authentication method, with the supplier’s cloud and retrieve all data to be stored in a relational database including wearables-collected information, questionnaires filled in by the participants and health data gathered by healthcare professionals. Health indices computed out of these data will be made available to participants in their website/app private areas, alongside trend graphics and other simple although insightful data visualizations of relevant information such as sleep pattern, accelerometry, pulse rate, pulse rate variability, among others. The system to be developed will also support the project throughout its course, namely by generating reports on its evolution (e.g., successful contacts), listing scheduled contacts, and asking participants to fill in questionnaires, among others.

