Strategies to reduce attrition during the experimental period will be implemented. At recruitment, pregnant women will be provided with detailed information about the project, including the objectives and participant’s role in the study. During post-allocation period, referrals to other healthcare professionals will be performed as necessary, and the required logistic support for data collection will be provided, such as scheduling suitable data collection appointments [69]. Reminders will be sent to enrolled women one week before the scheduled date of each data collection moment. Women in the intervention group with biomonitoring of physiological signals will receive tailored health-related information based on data collected through wearable devices (biofeedback), whereas women in both the control and intervention arms will receive general health information via a smartphone app (also accessible in the private area of the project’s website). This app will be developed specifically for MAMH@WORK project and will be available for download by all women enrolled in the study. It will mirror information available at the website and facilitate communication between the research team and participants. 

The main outcomes that will be used to assess the effectiveness of the intervention are women’s psychological wellbeing (mood disorders and anxiety disorders, assessed by the Hospital Anxiety and Depression Scale/HADS and by the Edinburgh Postnatal Depression Scale/EPDS), subjective wellbeing (Self-Report of Happiness), quality of mother–child interactions (assessed by the CARE-Index) and child-mother attachment (assessed by the Strange Situation Procedure and by the Postpartum Bonding Questionnaire/PBQ). Secondary outcomes include child emotional self-regulation and cognitive self-control; women’s job engagement and presenteeism; and women’s physiological signals (pulse rate, pulse rate variability, and sleep patterns).

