### 2.5. Statistical Analyses

Statistical analyses will be performed using IBM/SPSS 26.0 (or a more recent version at the time of data analysis) (IBM Corporation, NY, USA) [70] and R Software (R Foundation for Statistical Computing, Vienna, Austria) [71]. For all statistical analyses, the significance level will be set to α = 0.05.

Two strategies for data analysis will be performed: intention-to-treat (ITT) and per-protocol (PP) analyses. ITT considers all participants allocated to arms at the baseline, thus providing a more conservative estimate of the treatment effect, allowing for noncompliance and protocol deviations. In this case, the last observation carried forward method will be used to deal with missing data. PP analysis includes the subset of participants who completed all evaluations. Results from both types of analyses will be reported when comparing control and intervention groups. For effect size estimation, only PP results will be used, since these allow the identification of the treatment effect under optimal conditions, i.e., without major deviations from the protocol. Sensitivity analyses will be carried out to identify potential effects of data strata and missing data on the outcome.

Univariate description of sociodemographic and outcome variables will be performed by providing central tendency (mean and median) and dispersion (standard deviation and range) measures for each moment of data collection. Normality tests (Kolmogorov–Smirnov test or Shapiro–Wilk test) in combination with kurtosis and symmetry analyses will be used to assess the distribution of the variables under study. Levene´s test will be used to assess homoscedasticity. Baseline between-groups comparisons, i.e., control versus intervention groups, will be tested through ANOVA or its non-parametric equivalent (Kruskal–Wallis) for continuous variables, and chi-square test for categorical variables. Mixed model repeated measure (MMRM) analyses will be used for the analyses of main and secondary outcomes, comparing between control and intervention groups and adjusting for relevant covariates (including potential confounding factors). Mediation and moderation analyses will be explored using structural equation modelling. Conceptually and statistically relevant variables will be selected to adjust the models. The size of the intervention effect will be assessed by calculating Cohen’s *d* coefficient [98] Cramer’s V, and odds ratio.

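### The EPDS, a main outcome, is scheduled only after birth and so has no same-scale baseline; adding it at t0 would be a cheap gain in precision

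*Protocol article*

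**What the plan says.** Section 2.4 lists mood and anxiety disorders among the main outcomes, "assessed by the Hospital Anxiety and Depression Scale/HADS and by the Edinburgh Postnatal Depression Scale/EPDS". It sets five assessment times: t0 (28–30 weeks of gestation), t1 one week later, and t2, t3 and t4 at two weeks, five months and twelve months postpartum.

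Table 1 gives each instrument a timing label. The HADS ("HADS is a 14-item screening tool composed of two subscales, one for anxiety and other for depression") is labelled for pregnancy only and the EPDS for postpartum only. The same EPDS row says that "EPDS is a 10-item questionnaire that screens for depression in pregnant women and during the first postpartum year" and that the scale is validated in Portugal. Other rows (MHLS, CD-RISC, BRIEF COPE, the happiness item, EASAVIC) carry both labels, so the table does mark instruments that are used in both periods.

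Section 2.2 justifies recruiting in pregnancy on the ground that "antenatal depression is a relevant predictor for PPD [65,66". Section 2.5 states that "Mixed model repeated measure (MMRM) analyses will be used for the analyses of main and secondary outcomes", with adjustment for relevant covariates. It does not name the baseline score of the outcome among them.

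**The concern.** The protocol treats depression in pregnancy as prognostic for depression after birth, and it describes the EPDS as usable in both periods. Even so, it schedules no EPDS measurement in pregnancy. Two things follow for the EPDS analysis at t2, t3 and t4. The model cannot adjust for each woman's own EPDS level at entry, and the arms cannot be compared on that level at baseline.

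A baseline covariate that correlates with the outcome reduces the residual variance. In a trial of this size, that bears on whether a medium effect would be detected. A baseline that is not collected at t0 cannot be restored later by any analysis plan, so the choice has to be made before enrolment.

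**Working it through.** **Inputs from the protocol article.** Section 2.2 gives a minimum of 53 women per arm (159 in total), 75 per arm enrolled, attrition of about 40%, 80% power and a medium detectable effect. Section 2.5 gives a significance level of 0.05.

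**Assumptions.** The test is two-sided. A medium effect is taken as d = 0.5, because the article gives no number. The contrast is one intervention arm against control at one postpartum visit. The correlation r between the baseline covariate and postpartum EPDS is not in the documents. It is taken as 0.3 to 0.4 for t0 HADS depression and 0.5 for t0 EPDS. The HADS is assumed to be given at t0, since Table 1 says only that it is given in pregnancy.

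**The plan's own figure.** A total of 159 agrees with a three-arm one-way ANOVA at f = 0.25. The noncentrality is 159 × 0.25² = 9.94 on 2 and 156 degrees of freedom, which gives 80.5% power. That calculation uses no baseline adjustment. The means and standard deviations quoted in section 2.2 do not lead to 53 per arm. That is a separate matter, and nothing below depends on it.

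**Step 1: variance factor.** Adjusting for a baseline covariate multiplies the variance by 1 − r². This is equivalent to an effective sample size per arm of n/(1 − r²).

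- r = 0.3: 1 − 0.09 = 0.91; 53/0.91 = 58.2
- r = 0.4: 1 − 0.16 = 0.84; 53/0.84 = 63.1
- r = 0.5: 1 − 0.25 = 0.75; 53/0.75 = 70.7

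**Step 2: power.** Power comes from the noncentral t distribution with noncentrality 0.5 × √(n_eff/2) and 2·n_eff − 2 degrees of freedom. The second row set uses 45 per arm, which is 75 × (1 − 0.40).

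| Analysis of postpartum EPDS | Assumed r | Power, 53 per arm | Power, 45 per arm |
|---|---|---|---|
| No baseline covariate | – | 72.2% | 65.0% |
| Adjusted for t0 HADS depression | 0.3 | 76.3% | 69.2% |
| Adjusted for t0 HADS depression | 0.4 | 79.6% | 72.7% |
| Adjusted for t0 EPDS | 0.5 | 83.9% | 77.5% |

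**Step 3: the relevant difference.** Section 2.5 leaves room for the t0 HADS depression score as a covariate, so the comparator is the HADS-adjusted analysis.

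- 53 per arm: 83.9 − 79.6 = 4.3 points, or 83.9 − 76.3 = 7.6 points
- 45 per arm: 77.5 − 72.7 = 4.8 points, or 77.5 − 69.2 = 8.3 points

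If the two baseline scores have the same correlation with postpartum EPDS, the difference is zero.

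**The case against.** The strongest reply is that depression in pregnancy is measured, by the HADS depression subscale. Section 2.2 says that antenatal depression predicts postpartum depression; it does not say that an antenatal EPDS score does. Adjustment for relevant covariates can take in the HADS score. This stands. A reader might infer that the best baseline predictor of the main depression result is not collected, but nothing in the documents shows that the EPDS at 28–30 weeks predicts better than the HADS.

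The reply also limits the size. Setting an EPDS-adjusted analysis against a wholly unadjusted one gives power of 72% against 95% at r = 0.7, a gain of 23 points. That uses the wrong comparator and a high assumed correlation. Section 2.2 excludes women with a diagnosis of depression, a history of major depression or antidepressant treatment, which plausibly narrows the baseline range and lowers r.

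Three further readings are tempting and not supported:

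- **Mixing two scales.** One might infer that a single model from t0 to t4 would combine HADS and EPDS scores. Section 2.5 plans no such model, and the EPDS can be modelled over t2, t3 and t4.
- **Carry-forward.** A woman lost before t2 has no EPDS value to carry forward. A t0 EPDS carried forward would be a third-trimester score standing in for a postpartum one, so it would not give a valid value. The weakness there lies in the imputation method.
- **Bias.** Randomisation protects the postpartum comparison with or without a same-scale baseline.

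Finally, the visit schedule in Figure 1 is not shown, so the reading rests on Table 1. Its labels are coarse, but they are explicit for both scales and differ from those of the rows used in both periods.

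**Conclusion.** The point holds as a cheap improvement. It does not show an invalid analysis. As Table 1 stands, a main outcome has no baseline on its own scale, although the protocol itself describes the scale as suitable in pregnancy. What is lost is some precision and a same-scale check of balance between arms.

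Under the assumed correlations, the gain over adjusting for t0 HADS depression is about 4 to 8 points of power at d = 0.5. It could be nil if the EPDS predicts no better than the HADS. The figures describe one visit and one pairwise contrast, whereas the planned analysis is a repeated-measures model, so they indicate the order of the gain only.

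**What to change.** In Table 1, change the EPDS timing to cover both pregnancy and postpartum. Give it at t0, before allocation, in all three arms. In section 2.5, name the t0 EPDS score as the baseline covariate in the repeated-measures model of EPDS at t2, t3 and t4. If the EPDS cannot be added at t0, name the t0 HADS depression score as that covariate so that the choice is fixed in advance.

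The cost is ten more self-report items at an existing visit, with an instrument already validated in Portugal and already used in the trial. The fallback needs no new data, provided the HADS is given at t0.

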### 1.2. Aims and Objectives

The main aims of MAMH@WORK are: (a) to promote perinatal mental health, from the last trimester of pregnancy up to the first 12 months after childbirth, (b) to foster the healthy psychosocial and emotional development of children via an improved quality of early mother–child interactions, and (c) to reduce sickness absence and presenteeism of working-age women during this period. Considering these aims, the main goals of this project are to develop a maternal mental health and wellbeing promotion program and to evaluate its effectiveness. To achieve these goals, it is proposed the design, implementation and effectiveness assessment of a brief group cognitive-behavioral therapy-based (CBT-based) psychoeducation, including mindfulness e-training, combined with biofeedback. Specific objectives are to (a) design an intervention program to promote wellbeing and prevent perinatal mental disorders in Portuguese pregnant women; (b) develop a smartphone app that will provide women with targeted biofeedback based on the continuous (wearable-based) biomonitoring of selected physiological signals; and (c) assess the impact of the intervention on maternal perinatal mental health outcomes, on the interaction between mother and child (namely regarding the quality of mother–child interaction, child–mother attachment and child emotional self-regulation and cognitive self-control), and on the reduction of women’s absenteeism and presenteeism after childbirth.

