The RE-AIM (Reach, Effectiveness, Adoption, Implementation, and Maintenance) framework will be used to assess this evidence-based intervention in terms of its potential for translation and public health impact [68]. To assess the reach dimension of this project, the participation rate given as the proportion of invited pregnant women that accepted to participate in the intervention will be calculated. The effectiveness of the intervention will be assessed through a three-arm randomized controlled trial (Figure 1). The intervention group 1 will go through CBT-based psychoeducation sessions (including mindfulness e-training) by formally trained psychiatrists and psychologists; the intervention group 2 will benefit from the same CBT-based psychoeducation sessions (with mindfulness e-training) in addition to a biofeedback intervention; the control group will receive the care-as-usual from their health units. The development of a website for the project is planned and will include public and private areas. The public area will be accessible to the public and will contain information on mental health literacy, a description of the project’s objectives and its progress. Each participant allocated to the intervention arms will be provided with credentials to access her own private area. This area will contain personal, biomonitoring data (if applicable) and mindfulness e-training materials. Progressive Web Apps mimicking the website will be developed for smartphone use (Android and iOS).

Throughout the project, several physical and mental health outcomes will be measured and compared across groups. Since this intervention will be delivered by members of the research team, the adoption dimension (i.e., settings and staff that agree to deliver the intervention) does not apply in this case. However, the adequacy of the syllabus and a set of progress objectives (e.g., number of the psychoeducation intervention hours delivered, costs associated, and number of hours of online mindfulness exercises completed) will be used as a measure of its implementation. Finally, maintenance at both individual and setting levels will be measured at the last moment of data collection respectively by (a) the extent to which attendees maintain behavioral change after participating in the intervention and (b) the willingness of health unit managers to provide their users with this intervention.

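### Happiness, a main outcome, has a daily smartphone-app entry as its only stated source, so a woman who stops using the app loses it even if she attends every later visit

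*Protocol article*

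**What the plan says.** Section 2.4 lists "subjective wellbeing (Self-Report of Happiness") among the main outcomes used to judge effectiveness. Table 1 describes the measure as "Self-report single-item on happiness to be measured in a daily basis via the smartphone application", with timing in pregnancy and postpartum. Neither the text nor Table 1 gives another route.

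On timing, Section 2.4 says of data collection: "It will be conducted on five different moments". These are t0 (28–30 weeks), t1 (one week after enrolment), t2 (two weeks postpartum), t3 (five months) and t4 (twelve months).

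On the app, one objective in Section 1.2 is to "develop a smartphone app that will provide women with targeted biofeedback". Section 2.3 says of the website's private area: "This area will contain personal, biomonitoring data (if applicable) and mindfulness e-training materials". The apps reproduce the website. Section 2.4 makes the app available to all enrolled women, gives all arms general health information through it, and uses it for communication with the team. Only the biofeedback arm receives information tailored to its own signals.

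On analysis, Section 2.5 fills missing data in the intention-to-treat analysis by last observation carried forward. Of the per-protocol set it says: "PP analysis includes the subset of participants who completed all evaluations". Effect sizes come from that set alone.

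**The concern.** An outcome should be obtainable from every randomised woman, whether or not she keeps using what her arm offers. Here the stated record of a main outcome depends on continued use of an app that is also part of what the intervention arms receive. Loss of the outcome is thus tied to engagement, and the reasons to stay engaged are not the same in the three arms. Women whose mood is falling may be among those who stop entering data, although the article has no figures on this.

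At stake is the between-arm comparison of happiness. If stopping differs by arm and is related to happiness or its later course, the comparison is biased. The loss is also avoidable, because the same women are already due to complete questionnaires at the scheduled assessments. An answer that was never requested cannot be recovered by a later analysis.

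**Working it through.** **1. How the statements combine.**

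| Feature | What the article fixes | Where |
|---|---|---|
| Status | Main outcome | Section 2.4 |
| Route and frequency | App, daily | Table 1 |
| Trial collection moments | Five, t0 to t4 | Section 2.4 |
| App content, biofeedback arm | Own signals and tailored information, e-training, general information | Sections 1.2, 2.3, 2.4 |
| App content, psychoeducation arm | E-training, general information | Sections 2.3, 2.4 |
| App content, controls | General information, contact with team | Section 2.4 |
| Missing data, intention-to-treat | Last observation carried forward | Section 2.5 |

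Take a woman who stops using the app one month after birth but attends t3 and t4. On the stated route she gives no happiness answer at either. If a value is required there, her one-month entry is carried 5 − 1 = 4 months to t3 and 12 − 1 = 11 months to t4. The article does not say how daily entries become values at t0 to t4.

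**2. What the bias could be.** The article gives no rate of app use or stopping by arm. Its only attrition figure is about 40% overall (Section 2.2). The rates below are therefore assumptions. There is no true effect, and bias is intervention minus control, in SD of happiness.

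*Responders only.* If a share m stops and the tendency to keep responding correlates ρ with happiness, the responders' mean is shifted by ρ·φ(z_m)/(1 − m), where z_m is the normal quantile of m and φ the normal density.

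- m = 0.50: φ/(1 − m) = 0.399/0.50 = 0.798
- m = 0.30: 0.348/0.70 = 0.497
- with ρ = 0.5: 0.5 × (0.497 − 0.798) = −0.15

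*Carry-forward.* If happiness changes by T after stopping and the last entry is kept, the bias is T × (control stop rate − intervention stop rate). With T = −0.3: −0.3 × (0.50 − 0.30) = −0.06. With T = −0.5: −0.10.

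| Stopping, control / intervention (assumed) | Responders only, ρ = 0 to 0.5 | Carry-forward, T = −0.3 to −0.5 |
|---|---|---|
| 40% / 40% | 0 | 0 |
| 50% / 30% | 0 to −0.15 | −0.06 to −0.10 |
| 60% / 20% | 0 to −0.31 | −0.12 to −0.20 |

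A negative sign means the intervention looks worse than it is. The signs reverse if intervention women stop more often. Bias needs two things together: stopping that differs by arm, and a link between stopping and happiness or its trend.

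**The case against.** Several points on the other side stand.

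- **Differential stopping is not shown.** A reader might infer that app use will fall at different rates by arm. The article gives no such rates. Every enrolled woman can download the app, smartphone access is an inclusion criterion, and controls also use the app to communicate with the team. The supportable statement is that stopping may differ.
- **The app is not the whole intervention.** The core is 20 hours of group sessions (2 × 4 h plus 3 × 4 h, Section 2.3), held outside the app. Biofeedback and mindfulness material can also be reached on the website.
- **The per-protocol set is not shown to be near empty.** A reader might count 70–84 days to an assumed 40-week term plus 365 days, or 435–449 daily entries, and conclude that almost nobody completes them all. At an assumed 99% daily completion, with days independent, that gives 1.1% to 1.3%; at 99.9% over 435 days it gives about 65%. With five collection moments stated, the natural reading of a completed evaluation is t0 to t4. What remains is that the wording does not say so.
- **Figure 1 is not shown.** The assessment schedule may list happiness at the visits. The mapping of daily entries to visits may also sit in the full protocol or analysis plan.
- **Mitigations exist.** Section 2.4 plans reminders, Section 3 telephone contacts, and Section 2.5 mixed models and missing-data sensitivity analyses. These may reduce the loss or explore it, but none supplies answers that were not collected.
- **Reach is limited.** Happiness is one of several main outcomes and is not named among the main tools in the abstract. HADS, EPDS, PBQ, CARE-Index and the Strange Situation are unaffected.

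**Conclusion.** The point holds in a conditional form. In the text and Table 1, happiness is a main outcome whose only stated route is an app whose content differs by arm. Stopping the app ends the record even for women who remain in follow-up, and carry-forward would then substitute an old entry. The daily schedule and the five collection moments have not been reconciled.

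The size is unknown. It is zero in both models if stopping is equal across arms. It reaches about 0.15 SD (responders) or 0.10 SD (carry-forward) at assumed stopping of 50% against 30%, and about 0.31 or 0.20 SD at 60% against 20%, in either direction. These figures rest wholly on assumed rates, correlations and trends. The case for change rests on avoidable loss of a main outcome and a cheap remedy. It does not rest on any demonstrated imbalance.

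**What to change.** 1. Add the single happiness item to the scheduled questionnaires at t0, t1, t2, t3 and t4 for every woman in every arm, whether or not she uses the app. It must be answerable outside the app, since Section 2.4 has the project's own system prompting women to complete questionnaires.
2. Use those five values for the between-arm comparison of happiness.
3. Keep the daily app entries as supportive data.
4. State in Section 2.5 that daily entries do not count towards having completed the evaluations that define the per-protocol set.
5. Amend Table 1 to show both routes.

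The cost is one extra item per assessment and short wording changes, made before recruitment starts. The drawback is that the main comparison uses five values rather than a daily series. A team that values the daily series could argue for giving it more weight. That choice is secondary to collecting the scheduled answers from everyone.
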